# Comparison of 5-Day Multidaily Neuronavigated Theta-Burst Sessions With 6-Week Standard Repetitive Transcranial Magnetic Stimulation (the Dutch Depression Outcome Trial): Protocol for a Randomized Controlled Trial

**DOI:** 10.2196/70121

**Published:** 2025-08-21

**Keywords:** repetitive transcranial magnetic stimulation, rTMS, personalized accelerated intermittent theta-burst stimulation, personalized aiTBS, personalized functional connectivity–guided accelerated intermittent theta-burst stimulation, PAiT, Stanford neuromodulation therapy, SNT, functional magnetic resonance imaging, fMRI, dorsolateral prefrontal cortex, DLPFC, subgenual anterior cingulate cortex, sgACC, treatment-resistant depression

## Abstract

**Background:**

Novel therapies are crucial for patients with major depressive disorder, as more than 33% of patients do not respond to first-line treatments. A promising novel treatment strategy is an intensive 5-day course of personalized, functional connectivity–guided accelerated intermittent theta-burst stimulation (PAiT), modeled after the Stanford neuromodulation therapy protocol. This new form of repetitive transcranial magnetic stimulation (rTMS) may lead to higher remission rates in patients with treatment-resistant depression (TRD). However, it remains unclear how this accelerated strategy compares to the standard once-daily 10 Hz rTMS at inducing remission of depression.

**Objective:**

This study aims to compare cost-effectiveness using the PAiT protocol and the standard 10 Hz rTMS in patients with TRD.

**Methods:**

A total of 108 patients will be enrolled in this multicenter randomized controlled trial. Patients will receive stimulation over the left dorsolateral prefrontal cortex using either the PAiT protocol (10 sessions per day over 5 days, resulting in 50 sessions in total and 90,000 pulses) or standard 10 Hz rTMS (once daily for 6 weeks, resulting in 30 sessions in total and 90,000 pulses). Personalized targets will be identified in the accelerated intermittent theta-burst stimulation condition based on negative functional coupling between the subgenual anterior cingulate cortex and the dorsolateral prefrontal cortex. In the rTMS condition, the dorsolateral prefrontal cortex target locations are identified using the standard Beam-F3 method. In both conditions, coil placement is performed with neuronavigation, navigating either to the personalized functional connectivity target or the Beam-F3 location. Patients will undergo pre- and posttreatment functional magnetic resonance imaging scans, including cognitive and emotional tasks. Four follow-up assessments are scheduled at 7, 12, 26, and 31 weeks after baseline. We expect that the PAiT protocol is more cost-effective than the standard 10 Hz rTMS.

**Results:**

Recruitment for this randomized controlled trial started in February 2024. As of December 2024, we had enrolled 31 patients; the last participant is expected to complete their posttreatment assessments in January 2027.

**Conclusions:**

To our knowledge, this study is the first clinical trial to compare the cost- effectiveness of PAiT to standard 10 Hz rTMS as treatment for patients with TRD. The results of our study will offer professionals evidence from a sufficiently powered trial to determine whether the PAiT protocol is more effective than standard high-frequency rTMS. Specifically, it will assess whether PAiT leads to a shorter treatment duration for depression and greater societal or occupational participation among patients with TRD. In addition, this trial will provide further insights into the underlying mechanisms related to treatment effect, the effects of rTMS or accelerated intermittent theta-burst stimulation on cognitive domains such as executive functioning and emotion, possible differences in side effects, long-term effects, and factors contributing to possible relapse.

**Trial Registration:**

ClinicalTrials.gov NCT05900271; https://clinicaltrials.gov/study/NCT05900271

**International Registered Report Identifier (IRRID):**

DERR1-10.2196/70121

## Introduction

### Background

Novel therapies for depression are needed because more than 33% of patients with major depressive disorder are treatment resistant, that is, they do not respond sufficiently after treatment with 2 or more evidence‐based pharmacological or psychotherapeutic treatments [1]. Brain stimulation using repetitive transcranial magnetic stimulation (rTMS) or intermittent theta‐burst stimulation (iTBS), an alternative form of rTMS, has been shown effective with remission rates of 20% to 30% [2] in patients with treatment-resistant depression (TRD). rTMS and iTBS are noninvasive procedures, meaning that they do not involve surgery or general anesthesia. While the remission rates of rTMS and iTBS are lower than the 55% remission rate achieved by electroconvulsive therapy (ECT) [3], the most effective treatment for patients with depression, rTMS and iTBS have fewer side effects compared to ECT and antidepressant medication. Therefore, optimization of rTMS and iTBS therapies and their outcomes is a promising scientific goal.

### Novel Noninvasive Neuromodulatory Therapies

Transcranial magnetic stimulation (TMS), a noninvasive neuromodulatory therapy, has been added to the treatment arsenal for unipolar depression [4]. TMS is based on the principle of electromagnetic induction by applying magnetic pulses to the brain. This magnetic pulse induces an electrical field in the underlying neurons; when TMS pulses are applied repetitively, this effect outlasts the time of stimulation and leads to enduring effects on cortical excitability [5]. rTMS is recognized as a valuable therapeutic option in TRD [4]. Randomized controlled trials (RCTs) have consistently demonstrated the efficacy and safety of rTMS in TRD, with remission rates of approximately 25% [4,6-8]. In standard Food and Drug Administration–approved 10 Hz rTMS, 3000 pulses are given in 19 minutes; a train of 40 pulses lasting for 4 seconds is given every 15 seconds.

rTMS is not associated with common drug‐associated side effects (eg, nausea, sedation, akathisia, weight gain, and risk of intoxication) or the cognitive side effects often feared with ECT. The risk of developing side effects in response to rTMS is low [4,9]; transient headaches and localized scalp pain are the most common side effects and are self‐limiting or eminently treatable with paracetamol, acetaminophen, or other analgesics.

iTBS is a newer form of rTMS [10]. Magnetic pulses are applied in a certain pattern, called bursts. The basic element of theta-burst stimulation is a 3‐pulse burst at 50 Hz delivered every 200 ms (ie, 5 Hz). In the recently developed Stanford neuromodulation therapy (SNT) protocol, a train of 10 bursts lasting for 12 seconds is given every 10 seconds for 60 cycles in iTBS, resulting in a total session duration of 10 minutes. The main advantage of iTBS is that a similar number of pulses can be given in a shorter time frame [11,12]. This shorter time frame facilitates the administration of iTBS multiple times a day, contrary to the 24-hour spacing of standard 10 Hz rTMS [11,12]. Multiple daily iTBS sessions with adequate spacing of 50 minutes is likely to enhance the efficacy, as suggested by animal studies that showed hour‐long intervals may be optimal for producing long-term potentiation of neurons [13].

### Accelerated iTBS According to the SNT Protocol

There are 2 observational studies and 1 RCT on the SNT protocol (applying accelerated iTBS combined with functional magnetic resonance imaging [fMRI] task-based neuronavigation). The first observational study was a proof-of-principle study involving 6 participants [14]. The second study was a larger observational study [12]. The findings from a subsequent RCT resulted from the planned interim analysis [11]. These 3 studies reported an extremely high overall remission rate, at any point during the 4-week follow-up period, of 79% [15]. Dropout rates were low across all 3 studies; in the study by Williams et al [14], 1 of 5 patients dropped out due to lack of remission by day 4; in the observational study by Cole et al [12], 1 of 22 patients dropped out on day 1 of the trial due to a history of multiple therapeutic intolerances; and no participants dropped out in the RCT by Cole et al [11]. Overall, accelerated intermittent theta-burst stimulation (aiTBS) was well tolerated; reported side effects were similar to standard 10 Hz rTMS, that is, headache and scalp pain. No safety issues were reported. Although promising, it is unclear what the crucial element is of the SNT protocol: the intersession interval (ISI), accelerated delivery, high pulse dose, scalp-cortex correction, individualized targeting, or a combination of these factors.

The 50-minute spacing between sessions is in line with evidence from basic neuroscience research and human physiology data, showing that spaced iTBS sessions have an enhanced effect compared with the same number of single daily sessions [13]. Accelerated sessions, that is, more sessions per day, also contribute to nonlinear improvements in clinical symptoms. ISI of at least 50 minutes may enhance synaptic strengthening [12,13]. Finally, the functional connectivity–guided targeting method used in this study may have contributed to the high remission rate observed. The left dorsolateral prefrontal cortex (DLPFC) is a large brain area that consists of several subregions, some of which are correlated and some anticorrelated with subgenual anterior cingulate cortex (sgACC) activity. Recent studies suggest that these correlated and anticorrelated subregions are part of different affective circuits; stimulating a subregion of the left DLPFC that is anticorrelated with the sgACC reduces melancholic symptoms, resulting in lower depression scores [11,12]. This connection is not necessarily targeted with standard 10 Hz rTMS using the Beam-F3 method [16].

### Cost‐Effectiveness

No independent international studies exist that assess the cost‐effectiveness of SNT (as compared to standard rTMS) in the treatment of TRD. Given the patent restrictions on SNT, we sought to replicate SNT in our own personalized aiTBS protocol (personalized functional connectivity–guided aiTBS [PAiT]) to assess the cost-effectiveness of both treatments. Considering that treatment duration of the PAiT protocol is notably shorter compared to 10 Hz rTMS (1 week vs 6 weeks) and is expected to result in increased remission rates (ie, therefore obtaining more quality-adjusted life year benefits earlier), we will compare the 2 treatments on their cost-effectiveness to evaluate the potential added value of this innovative therapy for a more efficient health care system.

### Durability of the Effects of Personalized aiTBS

As of 2024, little was known about the long-term effects of personalized aiTBS. One could argue that the same remission or relapse course can be expected as for ECT, that is, quick antidepressant effects directly after the intensive 5-day treatment in combination with a high chance of relapse in the following weeks. Therefore, our study will have weekly clinical assessments for 7 weeks in both conditions to enable comparisons in treatment efficacy, during treatment, directly after treatment, and 1 week after treatment between rTMS and PAiT, along with follow-up clinical assessments at 6 and 25 weeks after treatment. In addition, we will investigate the (factors contributing to) side effects during the treatment in both conditions using an in-house questionnaire [17].

### Contribution to the Field of the Proposed Study

A well-powered and independent RCT is needed to determine the cost-effectiveness and safety of PAiT versus rTMS in patients with TRD.

## Methods

### Aim

The aim of the Dutch Depression Outcome Trial (D-DOTT) is to determine the cost‐effectiveness of PAiT versus standard daily 10 Hz rTMS in patients with TRD, who did not respond to 2 or more evidence‐based treatments, using an adequately powered RCT.

### Study Design

This multicenter single‐blind RCT consists of 2 phases in which participants will be randomly assigned to either standard 10 Hz rTMS (30 daily rTMS sessions in 6 weeks, providing a total of 90,000 magnetic pulses) or PAiT (50 iTBS sessions in 5 days, providing a total of 90,000 pulses) [11,12], with 4 follow‐up moments at 7, 12, 26, and 31 weeks after baseline. In either condition, the timing of these measurements translates to clinically relevant time points at 6 and 25 weeks after treatment, as well as aligned postbaseline follow-ups that are important for the cost-effectiveness analysis. As such, the follow-up measurement at 31 weeks after baseline is only used in the rTMS condition (25 weeks after treatment).

### Setting of the Study

This multicenter trial will take place within the Dutch specialized mental health care setting. Patients will be recruited from specialized outpatient clinics with ample experience in both the treatment of TRD and treatment with rTMS or iTBS, through self‐referral, and through the patient organization for depression (refer to the CONSORT [Consolidated Standards of Reporting Trials] flowchart in Figure 1)*.* Participating outpatient clinics are Radboudumc, GGZinGeest, Maastricht University Medical Centre+, and Amsterdam University Medical Centre. The following rTMS machines are used in this trial: MagStim Rapid2 (Amsterdam University Medical Centre, GGZinGeest, and Radboudumc), Neurosoft Neuro-MSX (Radboudumc), MAG and more powerMAG (GGZinGeest), and MagVenture MagPro X-100 (Maastricht University Medical Centre+). All sites use figure-of-8 coils. Localite is used for neuronavigation at all sites. The Neurosoft Neuro-MSX uses a built-in neuronavigation software.

**Figure 1 figure1:**
[figure not shown]
The CONSORT (Consolidated Standards of Reporting Trials) flowchart. UMC: University Medical Centre; MUMC: Maastricht University Medical Centre; rTMS: repetitive transcranial magnetic stimulation; PAiT: personalized functional connectivity–guided accelerated intermittent theta-burst stimulation.

### Participants

We aim to include 108 adult patients diagnosed with moderate to severe (Hamilton Depression Rating Scale >16) unipolar major depressive disorder without psychotic symptoms and who have had a failed response to at least 2 treatment trials with adequately dosed antidepressants or evidence-based forms of psychotherapy (interpersonal therapy, cognitive behavioral analysis system of psychotherapy, behavioral therapy, cognitive behavioral therapy, cognitive bibliotherapy, problem‐solving therapy, brief psychodynamic therapy, and reminiscence therapy). Exclusion criteria include lifetime diagnosis of bipolar disorder, current psychotic disorder, substance abuse disorder, suspected dementia, active suicidal thoughts with intent to act on them, patients with epilepsy, patients with large or ferromagnetic metal parts in the head (except for a dental wire), implanted cardiac pace maker or neurostimulator, or inability to understand or comply with study requirements.

These exclusion criteria serve 2 purposes: first, to ensure a clinically homogeneous sample of patients with unipolar depression, free from comorbid conditions that could affect treatment effectiveness; and second, to comply with safety guidelines related to rTMS, the accelerated iTBS protocol, and the required magnetic resonance imaging (MRI) procedures, as well as general safety standards.

### Study Procedures

Study information is provided to eligible participants, and these patients are contacted again after at least 7 days to discuss participation and any remaining questions. If patients choose to participate, they will be invited to a research intake session, during which they will sign the informed consent form and undergo screening for inclusion and exclusion criteria. Participation is voluntary, and individuals may withdraw from the study at any time. Table 1 shows an overview of the study. Participants who were allocated to standard 10 Hz rTMS will be offered PAiT after the end of the study (eg, 25 weeks after the last rTMS session). We will request patients allocated to PAiT to postpone enrolling in standard 10 Hz rTMS for 25 weeks after the last treatment session. This is merely a request as patients are allowed to ask for treatment as usual, including standard 10 Hz rTMS. Our participating treatment centers deem it not ethical to withhold this usual 10 Hz rTMS treatment upon a patient’s request. In addition to clinical effectiveness, we will study patient‐reported outcomes, tolerability, and safety. Alongside this RCT, we will also conduct an economic evaluation and evaluate facilitating and hindering factors related to implementation in the group of researchers and health care professionals involved in this study. The funding agency, the Efficiency Studies arm of the Care Research Netherlands and Medical Sciences of the Dutch Research Council, has explicitly requested that the trial be based in care as usual.

**Table 1 table1:** An overview of the study for both treatment conditions.

			rTMS^a^		PAiT^b^
**T0**					
	Week –2	Screening: clinicometrics; biobank; MRIc pre+additional tasks; rTMS premeasurements		Screening: clinicometrics; biobank; MRI pre+additional tasks; PAiT premeasurements	
**T1**					
	Week 0	Baseline		Baseline	
**T2**					
	Week 1	Treatment Clinicometrics (weekly)		Treatment Clinicometrics (daily)	
	Week 2	Biobank		Follow-up (1 week): clinicometrics (weekly); MRI post+additional tasks; biobank	
	Week 6	Clinicometrics		Clinicometrics	
**T3**					

	Week 7	Follow-up: clinicometrics; MRI post+additional tasks; biobank		Follow-up: clinicometrics; biobank	
**T4**					
	Week 12	Follow-up: clinicometrics; biobank		Follow-up: clinicometrics	
**T5**					
	Week 26	Follow-up: clinicometrics		Follow-up (25 weeks): clinicometrics	
**T6**					
	Week 31	Follow-up (25 weeks): clinicometrics		Clinicometrics	

^a^rTMS: repetitive transcranial magnetic stimulation.

^b^PAiT: personalized functional connectivity–guided accelerated intermittent theta-burst stimulation.

^c^MRI: magnetic resonance imaging.

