### Outcome Measures

#### Main Study Parameter or End Point

Remission of depression 1 week after the last treatment session was defined as a score of ≤7 on the 17-item Hamilton Depression Rating Scale (HDRS‐17).

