#### Secondary Outcomes

In addition to the primary outcomes, secondary outcomes will be assessed to provide a more comprehensive understanding of the effectiveness and impact of rTMS/PAiT. First, an economic evaluation based on the general principles of a cost‐effectiveness (utility) analysis, which will be performed alongside the intervention by comparing patients treated with PAiT with those receiving standard 10 Hz rTMS. In addition, societal costs and health consumption will be assessed for the economic evaluation at baseline and 7, 12, and 26 weeks after baseline. We will use health‐related quality of life determined with the EQ‐5D‐5L and health care use or costs, patients’ and their family’s out‐of‐pocket costs, and productivity losses owing to absenteeism measured with the Trimbos Institute and Institute for Medical Technology Assessment Cost questionnaire for Psychiatry [24]. Second, patient‐reported outcome measures will be recorded, that is, positive mental health, as measured with Mental Health Continuum‐Short Form [25] and subjective memory loss. Third, percentage reduction of depressive symptoms will be measured with self‐rated 9-item Patient Health Questionnaire (PHQ-9) on each treatment day and the HDRS‐17. Fourth, relapse will be measured at 6 and 25 weeks after treatment. Relapse was defined as an HDRS‐17 total score of ≥15 for 2 consecutive assessments separated by 5 to 15 days or hospitalization for depression. Fifth, we establish tolerability of the treatment and side effects of PAiT and rTMS [9]. Sixth, we will identify health care system–, clinician‐, and patient‐related factors that influence the implementation of PAiT were identified to inform the development of an implementation plan. Seventh, we will compare patient-reported changes in mood 1 week after treatment (as measured with self-rated PHQ-9) with clinician-reported clinical impression (as measured with Clinical Global Impression [23]).

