### Sample Size Calculations

Our trial should consist of 108 patients (for a 2‐sided test at α=.05 and with a power=0.80). Remission rates of patients treated with SNT in 2 open‐label studies and 1 interim analysis from an RCT were extremely high, that is, 79%. The remission rates in patients treated with ECT, the most well-known and effective treatment for TRD, is approximately 55% (range 48%‐65%). Our sample size calculation is based on the conservative assumption that our PAiT protocol is at maximum as effective as ECT in patients with TRD. For our sample size calculation, we used the 55% remission rate and the known remission rate for standard 10 Hz rTMS, 25%. We will oversample the necessary 82 patients with 32% to adequately handle possible attrition, as the new intervention will be relatively intense compared to standard 10 Hz rTMS treatment, resulting in a required sample size of 108 patients.

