For the Percentual reduction of depressive symptoms, as measured with self‐rated PHQ-9 on each day using the PAiT protocol, compared to weekly reduction of depressive symptoms, as measured with PHQ-9 during standard 10 Hz rTMS we will use linear mixed models. Similarly, we will determine percent reduction of depressive symptoms, as measured with the clinically assessed HDRS‐17 before, during, and after treatment, as well as at the follow-up moments.

Relapse, at 6 and 25 weeks after treatment, defined as (1) sustained remission, that is, HDRS-17≤7, and (2) sustained response, that is, response at end of treatment maintained through week 6 and 25. During treatment phase (T2), we will conduct the HDRS-17 weekly for 6 weeks for both treatment arms. By doing this, using the chi-square test, we can compare the remission rate with PAiT after 6 weeks to 6 weeks of treatment with standard 10 Hz rTMS; this is of interest as patients allocated to PAiT only receive treatment for 1 week.

We will report the prevalence of side effects during and directly after treatment based on international recommendation [17]. We will establish the tolerability and side effects of PAiT and rTMS. We will use qualitative data collected while supporting the implementation of PAiT, to analyze health care system–, patient‐, and clinician‐related factors that influence the implementation of PAiT in clinical settings. We will use a 1-tailed paired *t* test or an ANOVA to compare patient-reported changes in mood 1 week after treatment (as measured with self-rated PHQ-9) with clinician-reported clinical impression (as measured with the Clinical Global Impression scale).

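### PAiT patients may take standard rTMS after their 5 days, and under intention-to-treat the week-6 and durability outcomes credit its benefit to PAiT

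*Protocol article*

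**What the plan says.** **Access to the comparator (Study Procedures).** Patients allocated to PAiT are asked to wait 25 weeks after their last session before standard 10 Hz rTMS. The next sentence reads: "This is merely a request as patients are allowed to ask for treatment as usual, including standard 10 Hz rTMS". The centres consider it unethical to withhold rTMS from a patient who asks, and no minimum wait is stated. Patients allocated to rTMS are offered PAiT after the end of the study.

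**Week-6 comparison (Secondary Study Parameters).** Remission at 6 weeks is compared between arms by a chi-square test. The stated reason is that "this is of interest as patients allocated to PAiT only receive treatment for 1 week".

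**Durability (Secondary Outcomes; Secondary Study Parameters).** Relapse is an HDRS-17 total of 15 or more "for 2 consecutive assessments separated by 5 to 15 days or hospitalization for depression". At 6 and 25 weeks after treatment, sustained remission is HDRS-17 of 7 or less, and sustained response is "response at end of treatment maintained through week 6 and 25". The section on durability in the Introduction motivates these outcomes by the risk of relapse after a short intensive course.

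**Analysis sets (Statistical Analyses, Overview).** Both intention-to-treat and per protocol samples are analysed. The only stated rule for a failed course concerns missed sessions (Challenges of the Proposed Trial).

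**The concern.** Starting the comparator treatment is not an event in any of the outcome rules. Under intention-to-treat, two kinds of PAiT patient are then scored in PAiT's favour because of rTMS:

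- A non-remitter who takes rTMS and reaches HDRS-17 of 7 or less counts as a PAiT remission at later visits.
- A remitter or responder who relapses between two widely spaced visits, or is about to relapse, and is brought back or held by rTMS counts as sustained.

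Sustained response requires response at the end of treatment, so late converts cannot enter it. There only the second route applies.

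The rTMS arm has no matching route to PAiT during follow-up, so the bias has a known direction. At stake are the time-matched comparison and the claim that one week of PAiT has lasting effects. The scored outcome would instead describe PAiT followed by rTMS on request.

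**Working it through.** **1. The plan's own sample size.** Inputs from Sample Size Calculations: two-sided "test at α=.05 and with a power=0.80", and rates of 55% and 25%. With the pooled-variance formula for two proportions (mean rate 0.40):

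n per arm = [1.960 × √(2 × 0.40 × 0.60) + 0.842 × √(0.55 × 0.45 + 0.25 × 0.75)]² / 0.30² = (1.358 + 0.555)² / 0.09 ≈ 40.7, so 41 per arm and 82 in total.

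82 × 1.32 = 108.2, so 108. The stated figures reproduce. They rest on "Remission of depression 1 week after the last treatment session", which falls at about week 2 in the PAiT arm and leaves almost no time for later rTMS to act. This point does not touch them.

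**2. Inflation of later PAiT remission.** Let p be PAiT's own remission rate, q the share of non-remitters who start rTMS, and 0.25 the protocol's rTMS remission rate. The article gives no q; 20-60% is assumed.

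Inflation = (1 − p) × q × 0.25

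| p | q = 20% | q = 60% |
|---|---|---|
| 55% | 0.45 × 0.20 × 0.25 = 2.3 points | 0.45 × 0.60 × 0.25 = 6.8 points |
| 25% | 0.75 × 0.20 × 0.25 = 3.8 points | 0.75 × 0.60 × 0.25 = 11.3 points |

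With 54 per arm this is 1.2 to 3.6 patients at p = 55%, and 2.0 to 6.1 at p = 25%.

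**3. How much applies at week 6.** PAiT ends in week 1 and its primary assessment is at about week 2. A patient who starts rTMS then has about 4 weeks of a 6-week course by week 6, and at most about 5 if it starts straight after PAiT. The figures in step 2 are therefore upper bounds at week 6. A full course fits well before week 26.

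**4. Error rate of the week-6 test if the arms are truly equal.** Take 25% in both arms, 54 per arm, and a pooled chi-square test at two-sided 5%. The apparent PAiT rate is 0.25 + 0.75 × q × 0.25.

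| q | Apparent PAiT rate | Probability of rejection |
|---|---|---|
| 0 | 25.0% | 4.9% |
| 20% | 28.8% | 7.1% |
| 40% | 32.5% | 13.6% |
| 60% | 36.3% | 24.4% |

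These values use the full-course inflation, so they too are upper bounds at week 6. The article specifies no remission chi-square test after week 6 to which they would apply in full.

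**5. Sustained remission.** Assume 30-50% of PAiT remitters relapse, 20-60% of those take rTMS and 25-50% remit again.

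- Low: 0.55 × 0.30 × 0.20 × 0.25 = 0.8 points, or 0.4 of 54 patients.
- High: 0.55 × 0.50 × 0.60 × 0.50 = 8.3 points, or 4.5 of 54 patients.

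This counts every relapse. HDRS-17 is rated weekly to about week 7 and again at week 12, so earlier relapses would usually be seen. Only those between the week-12 and week-26 visits would usually be missed. Completing a 6-week course before week 26 also means starting it by about week 20 (26 − 6). The range of about 1-8 points is an upper bound.

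**The case against.** **The article never says that remissions after rTMS count for PAiT.** True. It follows from analysis by allocation on HDRS-17 scores with no other rule. A per protocol sample is also named, and an unseen analysis plan may exclude patients who start rTMS. That limits how firmly the point can be put. It does not remove it, because the outcome definitions given in the article, followed as written, produce the bias under intention-to-treat.

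**The two sections need not contradict each other.** A reader might infer a flat contradiction between one week of treatment and rTMS on request. The one-week remark can equally be read as describing allocated treatment, with rTMS being usual care afterwards, and the request to wait 25 weeks will reduce uptake. This stands. The passages need reconciling, but the stronger charge is not supported.

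**As-observed results suit a care-as-usual trial.** The stated aim is cost-effectiveness, and the funder asked for a trial based in usual care. This stands for the cost-utility analysis, where added rTMS belongs in both the costs and the effects of starting with PAiT. It is weaker for outcomes presented as the durability of a one-week course.

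**Counting rTMS as an event could tilt the other way.** Non-trial rTMS is expected mainly in the PAiT arm, medication changes are not counted in either arm, and a patient who starts rTMS while well would be scored as an event. This stands, and is why both results should be shown.

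**The numbers are assumed.** Uptake has no basis in the article. A 25% remission rate may be generous for patients who have just failed stimulation of the left DLPFC. This stands, so the sizes are given as ranges and upper bounds.

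**Conclusion.** The concern holds for secondary outcomes. Access to the comparator is one-sided, and the week-6 and durability outcomes cannot tell its benefit from PAiT's. The direction favours PAiT. With 20-60% uptake among non-remitters and 25% remission on rTMS, both assumptions about this setting, later PAiT remission is raised by at most about 2-7 points at an own rate of 55%, or 4-11 points at 25%, and by less at week 6.

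Three stronger inferences are not supported:

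- That the trial's main result is biased: the primary endpoint comes one week after the last session, and the sample size is unchanged.
- That the week-6 test has a true error rate of 7-24%: those values assume a full rTMS course that does not fit by then.
- That sustained remission is overstated by as much as 8 points: this would need relapses that the weekly and week-12 visits would usually detect.

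The plan should be changed before analysis, but the point does not threaten the trial's main conclusion.

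**What to change.** 1. Reconcile the one-week rationale in Secondary Study Parameters with the access described in Study Procedures.
2. Record the start date of any non-trial rTMS or ECT in both arms.
3. For relapse, sustained remission and sustained response, count such a start as relapse or loss of sustained status from that date. Report the as-observed (treatment-policy) result alongside.
4. Report the week-6 comparison both ways.
5. Report uptake of non-trial rTMS and ECT by arm and over time.
6. Leave the cost-utility analysis as observed.

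**Cost.** This is analysis wording plus one data item; patients' access to treatment does not change. The article describes resource-use questionnaires at baseline and weeks 7, 12 and 26 with a 3-month recall, but does not say that start dates are captured. A field may have to be added and completed retrospectively for patients already enrolled (31 by December 2024). PAiT's durability figures become slightly less favourable, and a patient who starts rTMS while still in remission is scored as an event.
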